### Anthropometrical Assessments

For participant characteristics and calculation of BMI, standardized procedures and equipment will be used to measure participant height (cm) by stadiometer Seca 213 (seca) and body weight (kg) by a bioelectrical impedance (BIA) Tanita BC-418 MA Multi-Frequency segmental body composition analyzer (Tanita) [47]. Data on body composition will be given to the participants as an incentive to join the study but will not be included in future data analysis.

### Photo and Narrative Documentation of Organizational Factors

The Stanford Healthy Neighborhood Discovery Tool smartphone app (Discovery Tool), based on the Our Voice citizen science framework [39], will be used during the fifth workshop of the sustainable and healthy intervention to document elements in the physical and organizational environment that either help or hinder employees’ attempts to be active and eat in healthy ways at work. Participants in the intervention arm will be instructed to take photos of barriers and facilitators for a sustainable lifestyle at or near the office, whereas the control arm will document barriers and facilitators for a healthy lifestyle, for 1 week. The app prompts the participants to add a text narrative explaining each photo. This makes it possible to highlight positive and negative aspects of the work environment, as well as suggest improvements and things that are missing. The participants can also leave a reaction to the photo in the form of positive or negative smiley faces. After taking photos, the participants upload the photos and accompanying Discovery Tool data to a secure server at Stanford University in anonymized form. From there, study personnel will access the data and download it to a local server at Mälardalen University. The participants in both intervention arms will discuss the photos at the sixth workshop of the intervention and create a list of 3-4 prioritized actions to be made until the follow-up workshop 7, which is 2-3 months after the intervention. This way, the participants can impact their everyday environment on an organizational level to facilitate a sustainable and healthy lifestyle, respectively. Discussions and comments during the workshops will be noted and transferred to electronic format. The analysis of photographs, audio narratives (voice-to-text), and additional comments are to be analyzed through the “By the People” Our Voice citizen science method [48-50], followed by a content analysis [51] to quantify and analyze the presence, meanings, relationships of certain words, themes, or concepts. One of the research team members will take the lead in coding, which will be reviewed and discussed by the remaining team members. Thus, the “Our Voice” method amplifies the voices and perspectives of participants throughout the scientific process [52], which ensures the trustworthiness and credibility of the results.

### Statistical Analyses

Data analysis will be performed according to the intention-to-treat principle [53], and all quantitative data will be analyzed using R statistics (R Foundation for Statistical Computing). Linear mixed-effects models [54] are planned for the analysis of intervention effects for numerical variables with a Gaussian distribution. These models are particularly suitable for repeated measures and can adeptly handle unbalanced groups. Linear mixed-effects incorporate both fixed and random effects, providing a robust method for accurately representing nonindependent data structures. For numerical variables with non-Gaussian distributions, the analysis will be conducted using generalized linear mixed-effects models. Generalized linear mixed-effects models are an extension of the generalized linear model in which the linear predictor contains random effects in addition to the usual fixed effects [54,55].

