## Methods

### Study Design and Sample Size

The SOFIA study is part of a larger mixed-method effort titled *Concepts for the Sustainable Office of the Future* (SOFCO) [24], which is studying how sustainable lifestyles and health may be supported among office workers in Sweden. Here, we describe the SOFIA substudy, which is a 2-arm, single-blind (participants), cluster randomized controlled trial comparing a sustainable lifestyle intervention arm with a healthy lifestyle control arm (Figure 1). The intervention study, which will occur in office sites in the Mälardalen region, Sweden, runs over 8 weeks, with each intervention consisting of 6 workshops occurring every week for the first 4 weeks and then every second week for the last 4 weeks (Figure 2). The data collection will occur at baseline and after 4 and 8 weeks, with the target number of randomly assigned participants per intervention arm being 47 participants each.

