### Study Population

The project is being conducted in collaboration with companies in the office sector in Sweden. Company A owns and develops office buildings, is located in a medium-sized city, and houses approximately 35 office workers. Company B coordinates and develops facility management, is located in a large city, and has approximately 400 office workers. Through advertisement at these offices, we will invite office workers to sign up via a short web-based screening questionnaire to confirm eligibility for the study, the number of hours working in their office per week, the office location, and active commuting and food habits, along with their contact information. The questionnaire takes approximately 2-5 minutes to complete and will be administrated using links and QR codes. Eligible study participants are aged 18-65 years and perform office work ≥20 hours per week. Exclusion criteria comprise not having access to a smartphone compatible with the Discovery Tool (such as iPhone 5 or Android 2, 3, or later versions), being blue-collar workers who perform ≥20 hours per week of strength or physical work rather than office work, having mental disabilities, and not speaking Swedish.

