### Power Calculations and Randomization

Participants working in the targeted offices will be cluster-randomized based on the office’s geographic location by using a computer-generated random number generator in the statistical software R version 4.3.2 or later (Multimedia Appendix 5) [56]. Based on simulations derived from the pilot study CLEAR 2018 (unpublished data) using diet-related CO_2_e expressed as kg/day/person derived from Meal-Q, where we have an effect size of *η*^2^=0*.*11 for the interaction, a sample size of 40 observations in each arm at each assessment is indicated for 80% power. The estimated sample size was based on the interaction effect between control and intervention arms on CO_2_e in a linear mixed model maintaining a significance level of 5% from the CLEAR 2018 study. We assume a dropout rate of 10% to 15% after baseline assessment, and therefore, we will recruit 47 people to each arm, in order to have at least 40 at the end of the study. If the dropout rate in this study is less than 10%, no particular method will be used to account for attrition.

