### Primary Objective

The primary objectives are to examine the amount of change in the consumption of nutrients (fat, protein, carbohydrates, and fibers), more climate-friendly foods (increased intake of plant-based food and less dairy, red and processed meat, diet-related CO_2_e), more organic food, and increased practice of active transportation and related environmentally friendly behaviors. This will be evaluated by studying 1 variable at a time plus creating aggregated variables (the sums of all servings of fruits and vegetables expressed as servings per day), as well as creating a Sustainable Lifestyle Index, where each variable will be scored and summed to derive an overall score for each person [57], where higher scores indicate a more sustainable lifestyle. Finally, we will study the excretion of pesticide residues in urine as a validation of the consumption of organic food and explore if the excretion differs between the arms after the 8-week intervention.

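### Office locations are randomised, but the stated mixed model is not tied to them; if office is left out of the analysis, p-values will be too small

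*Protocol article*

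**What the plan says.** Study Design and Sample Size describes SOFIA as a trial "which is a 2-arm, single-blind (participants), cluster randomized controlled trial". Power Calculations and Randomization fixes the unit: "Participants working in the targeted offices will be cluster-randomized based on the office’s geographic location".

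The Statistical Analyses section then gives the method: "Linear mixed-effects models [54] are planned for the analysis of intervention effects for numerical variables with a Gaussian distribution". Generalised linear mixed models are to be used for non-Gaussian numerical variables. Two specific reasons are given, repeated measures and unbalanced arms: "These models are particularly suitable for repeated measures and can adeptly handle unbalanced groups". A more general phrase follows, that fixed and random effects are combined, "providing a robust method for accurately representing nonindependent data structures". No random effect is named for person or for office, and the section does not mention office, cluster or intraclass correlation.

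The sample size rests on an interaction effect on diet-related CO2e in a linear mixed model, with η² = 0.11, a 5% level and 80% power. This gives 40 observations per arm at each assessment, raised to 47 per arm for dropout. No design effect, cluster size or number of clusters is stated.

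**The concern.** Participants in one location are allocated together, so the evidence on the arm effect comes from the number of locations as well as the number of people. The intervention also builds in dependence. According to the Procedure section and the section on photo and narrative documentation, workshops are held in person at or near the workplace, and each group discusses its photos and agrees a short list of joint actions. The Results section reports groups of 5 to 15 per arm and iteration. Change over eight weeks may well be more alike within a group than between groups.

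If the fitted model has only a participant effect, it allows for correlation between one person's three assessments but treats colleagues as independent. The standard error of the arm contrast is then too small, and so are the p-values. The number of offices is not given. Participants come from two companies, one with about 35 office workers and one with about 400, so there may be few locations. Large-sample tests would then be unreliable even with a cluster term in the model.

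**Working it through.** **1. The plan's own figure.** Inputs from Power Calculations and Randomization: η² = 0.11, level 5%, power 80%, 40 per arm. There are three assessments (Study Design and Sample Size). I take the interaction to be arm by time, although the article does not name the second factor.

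- f² = 0.11 / (1 − 0.11) = 0.1236.
- With N independent participants: numerator df = 2, denominator df = 2(N − 2), noncentrality λ = f² × N.
- N = 80: λ = 0.1236 × 80 = 9.89, df 2 and 156, power 80.3%.
- N = 78: power 79.2%.

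The smallest N that reaches 80% is 80, or 40 per arm. The stated figure reproduces exactly with no allowance for clustering. With denominator df of N − 3 the answer is 41 per arm, which leads to the same conclusion.

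**2. Type I error if office is omitted.** The cluster size m and the intraclass correlation for change, ρ, are assumptions. I use the reported group size of 5 to 15 as a proxy for m.

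- Design effect: DE = 1 + (m − 1)ρ.
- True error of a nominal 5% one-df person-level test: 2 × [1 − Φ(1.96 / √DE)].

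For m = 8 and five groups per arm (40 per arm):

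| ρ | DE | 1.96/√DE | Formula | Simulated, person-level | Simulated, cluster means |
|---|---|---|---|---|---|
| 0.01 | 1.07 | 1.895 | 5.8% | 5.8% | 5.0% |
| 0.05 | 1.35 | 1.687 | 9.2% | 9.3% | 5.0% |
| 0.10 | 1.70 | 1.503 | 13.3% | 13.5% | 5.0% |

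The simulation drew change scores under no arm effect (100,000 runs per row). It compared a t test on persons with a t test on cluster means.

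Other layouts by the same formula:

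- m = 5, ρ = 0.01: 5.5%.
- m = 10, ρ = 0.05: 10.4%.
- m = 15, ρ = 0.10: 20.6%.

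**3. Why an office intercept alone is not enough.** Write the office part of an outcome at time t as u + w(t), with u constant over time. The change from baseline to week 8 contains (u + w(8)) − (u + w(0)) = w(8) − w(0). The intercept u cancels. The variance that matters for an arm-by-time test is that of w, the office-by-time term.

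**4. Effect on power.** Dividing λ by DE at 40 per arm and m = 8:

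- ρ = 0.01: λ = 9.89 / 1.07 = 9.24, power 77%.
- ρ = 0.05: λ = 9.89 / 1.35 = 7.32, power 67%.
- ρ = 0.10: λ = 9.89 / 1.70 = 5.82, power 56%.

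Over m = 5 to 15 and ρ = 0.01 to 0.10, power runs from 79% to 42%. The number of completers needed for 80% runs from 42 per arm (40 × 1.04, rounded up) to 96 per arm (40 × 2.40). None of these figures includes the further loss from having few clusters.

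**The case against.** The strongest reply is that the section does not restrict the random effects to persons. Its phrase about nonindependent data could include offices. The article is condensed, and random-effect terms are commonly left to an analysis plan that is not shown. The reproduced sample size shows how the trial was sized, not how it will be analysed. The simulated person-level t test is not a method the article proposes.

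Much of this stands. The article does not show that office will be omitted, so the point must be conditional. The list of effects is not faulted for being short. What remains is a mismatch inside the article: the design randomises locations, the specific reasons given for the model do not include them, and the one quantified use of such a model matches independent participants.

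A reader might also infer that the plan gives up a baseline-adjusted comparison at week 8, or ignores baseline urine because the Primary Objective section says it will "explore if the excretion differs between the arms after the 8-week intervention". The text does not support either reading. No contrast is named, and an arm-by-time model that includes baseline among the repeated measures contains a week-8 contrast against baseline. The urine sentence states a question, not a model, and urine is collected at both times. Nor do the documents give the number of clusters or say that each arm had a single group per iteration.

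**Conclusion.** The point holds in conditional form. As written, the analysis is not tied to the randomised unit. If office is omitted and change is correlated within office, p-values will be too small and confidence intervals too narrow. The inflation is about one percentage point at an assumed correlation of 0.01, and the error rate reaches about 9% to 14% at 0.05 to 0.10 with five groups of eight per arm. It worsens with fewer, larger clusters. These sizes rest on assumed values for the correlation, cluster size and number of clusters, none of which the article supplies. The direction of the error needs only a positive correlation. Because this affects the validity of the main comparison, it should be settled before the full trial is analysed. Recruitment is still continuing, so there is time.

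**What to change.** State in the Statistical Analyses section that the arm effect on change is analysed at the level of the randomised office, by one of two routes:

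- **Gaussian outcomes with enough offices:** a mixed model with random effects for participant, office and office-by-time, and a small-sample degrees-of-freedom correction.
- **Few offices, or non-Gaussian outcomes:** an analysis of baseline-adjusted office means on (offices − 2) df, reduced by one for each cluster-level covariate such as company. A small-sample correction of the first kind is not routinely available for the planned generalised models. With one office per arm this leaves 2 − 2 = 0 df, and the office effect cannot be separated from the arm effect.

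Give the number of offices and an assumed intraclass correlation, and say which route applies at which number.

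The change needs only wording and R code, but precision is lost. With ten groups of eight and ρ = 0.05, the interval widens by a factor of about √1.35 × 2.306/1.991 = 1.35 (t quantiles on 8 and 78 df). Power at 40 per arm falls below the stated 80%.

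As an option, use the baseline values already collected, including urinary pesticide per gram of creatinine, as covariates. Compared with change scores, this multiplies the variance by (1 + r)/2, which is 0.80 at an assumed baseline to week-8 correlation of r = 0.6. This is a gain in efficiency, not the correction of an error.

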### Power Calculations and Randomization

Participants working in the targeted offices will be cluster-randomized based on the office’s geographic location by using a computer-generated random number generator in the statistical software R version 4.3.2 or later (Multimedia Appendix 5) [56]. Based on simulations derived from the pilot study CLEAR 2018 (unpublished data) using diet-related CO_2_e expressed as kg/day/person derived from Meal-Q, where we have an effect size of *η*^2^=0*.*11 for the interaction, a sample size of 40 observations in each arm at each assessment is indicated for 80% power. The estimated sample size was based on the interaction effect between control and intervention arms on CO_2_e in a linear mixed model maintaining a significance level of 5% from the CLEAR 2018 study. We assume a dropout rate of 10% to 15% after baseline assessment, and therefore, we will recruit 47 people to each arm, in order to have at least 40 at the end of the study. If the dropout rate in this study is less than 10%, no particular method will be used to account for attrition.

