### Research Hypothesis

The study hypothesis is to investigate whether providing information about sustainable living encourages individuals to adopt more nutritious dietary habits and increase their levels of physical activity, as compared to receiving information solely centered around health-related recommendations for dietary intake and physical activity. The hypothesis will be tested among office workers to explore the workplace as an arena for health promotion.

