## Discussion

### Principal Findings

This study aims to increase the understanding of the effectiveness of promoting a sustainable lifestyle to motivate behavioral change toward more nutritious food habits and increased physical activity, as compared to providing information based exclusively on health-related arguments in line with recommendations for food habits and physical activity. By targeting motivation, capabilities, and opportunities based on the behavioral change wheel model [58], we intend to increase the effect of the intervention in this specific context; moreover, it improves the understanding of behaviors in relation to the workplace environment [32]. A potential primary finding of this study would be that the intervention arm that received information about a sustainable lifestyle improved their food habits and physical activity level equally, or more, as compared to the control arm receiving information about health-related recommendations. Additionally, it is anticipated that the study will show that a shift to a sustainable lifestyle will lower diet-related CO_2_e emissions and reduce the excretion of urinary residuals of pesticides to a larger degree in the intervention arm than in the control arm.

A novel feature of this study is the use of the workplace as an arena for health promotion, and in particular office workers, a group known to be sedentary at work [59]. A substantial proportion of the adult population spends a significant amount of time at work each day, and the advantage of an office-based intervention is that many individuals can participate simultaneously at work [23,60]. Moreover, from the employee’s perspective, these types of interventions are convenient and easily accessible and allow employees to interact and support each other in their efforts to undertake behavior changes [61]. Full-time employees spend up to 60% of their waking hours at work [62] and typically return repeatedly to the same location, providing a significant opportunity to deliver health interventions. Recent review articles show that multicomponent workplace dietary interventions are effective but also an unutilized area to positively influence dietary intake and health outcomes among office workers [63]. However, the intervention needs to be tailored to the workplace and use behavioral and cognitive strategies to be successful [64,65]

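### The research hypothesis (more nutritious diet, more physical activity) and the sample-size basis (diet-related CO2e) do not match, so the hypothesis as written has no sized test

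*Protocol article*

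**What the plan says.** **Question.** The Research Hypothesis section asks whether information about sustainable living "encourages individuals to adopt more nutritious dietary habits and increase their levels of physical activity" more than purely health-based information does. The abstract's Objective puts the same question. Neither mentions CO2e.

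**Sizing.** Power Calculations and Randomization contains the only sample-size calculation. Its variable is diet-related CO2e, "expressed as kg/day/person derived from Meal-Q", with eta-squared 0.11 taken from an unpublished pilot study. It concludes that "a sample size of 40 observations in each arm at each assessment is indicated for 80% power", and adds: "The estimated sample size was based on the interaction effect between control and intervention arms". Recruitment is set at 47 per arm to allow for dropout. No effect size or power is given for any nutrient or activity variable.

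**Primary list.** The Primary Objective section names macronutrients and fibre, climate-friendly foods including diet CO2e, organic food, active transportation and related behaviours, and a Sustainable Lifestyle Index. It singles none of them out. Overall physical activity is not on the list, although Active-Q measures it.

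**Expected findings.** Principal Findings gives food habits and physical activity level as the potential primary finding. CO2e comes after it: "Additionally, it is anticipated that the study will show that a shift to a sustainable lifestyle will lower diet-related" CO2e.

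**The concern.** The hypothesis concerns nutrition and activity, while the calculation concerns the carbon footprint of food. A lower footprint is not in itself a more nutritious diet, and it says nothing about activity. The mismatch is separate from the number of variables tested: if CO2e became the sole primary variable tomorrow, the hypothesis as worded would still have no sized test.

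At stake is how the final results are read. The protocol gives no basis for judging how informative a nutrition or activity comparison would be at this sample size. It also does not say which variables would count as an answer to the hypothesis.

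**Working it through.** **1. Inputs**
- From Power Calculations and Randomization: eta-squared 0.11 for the interaction; 40 per arm (N = 80); 80% power; "in a linear mixed model maintaining a significance level of 5% from the CLEAR 2018 study".
- From Study Design and Sample Size: "The data collection will occur at baseline and after 4 and 8 weeks". This makes three assessments and so 2 degrees of freedom for an arm-by-time interaction.
- Assumed: the interaction is arm by time, tested by an F test, with participants independent.

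**2. Reproducing the planned figure**
- f² = 0.11 / (1 − 0.11) = 0.1236.
- Noncentrality λ = N × f² = 80 × 0.1236 = 9.89.
- Noncentral F, numerator df 2, 5% level: power 0.795 with 78 denominator df and 0.803 with 2 × (80 − 2) = 156.
- With 2(N − 2) denominator df, 40 is the smallest number per arm that reaches 80%.
- Dropout: 40 / 0.90 = 44.4 and 40 / 0.85 = 47.06; conversely 47 × 0.85 = 39.95. Recruiting 47 is consistent with the stated range.

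The arithmetic is sound for CO2e under independence.

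**3. Can CO2e stand in for the hypothesis?**
- *Activity:* no. Questionnaire Data defines CO2e from a life-cycle carbon value attached to each food item in Meal-Q. No Active-Q information enters it.
- *Nutrition:* the protocol does not claim it. Comparison to Prior Work describes a diet trial in which healthier choices were expected to lower CO2e and no difference between arms was found.
- *Transfer of the effect size:* not shown. The arms differ by design on climate content (low-CO2e recipes, less red and processed meat). They overlap on nutrition and activity, since both receive the Nordic dietary advice and WHO activity advice. A smaller contrast on the hypothesised outcomes is plausible but not established, because the intervention arm also gets extra advice on active transport and breaking up sitting.

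**4. What 40 per arm gives at other effect sizes**

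The protocol has no effect size for nutrition or activity, so these are assumed values, from the same formula:

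| eta-squared | λ = 80 × f² | power |
|---|---|---|
| 0.11 (protocol, CO2e) | 9.89 | 0.80 |
| 0.06 | 5.11 | 0.50 |
| 0.03 | 2.47 | 0.26 to 0.27 |
| 0.01 | 0.81 | 0.11 |

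For a plain comparison of two means, the standardized difference detectable with 80% power is (1.96 + 0.84) × √(2/40) = 0.63.

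**5. Clustering**

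Allocation is by office location, and the reproduced figure makes no allowance for it. As an illustration, take an assumed 10 people per cluster and design effect 1 + 9 × ICC, and divide λ by it (156 denominator df):

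| assumed ICC | design effect | λ | power at eta-squared 0.11 |
|---|---|---|---|
| 0.01 | 1.09 | 9.07 | 0.77 |
| 0.05 | 1.45 | 6.82 | 0.63 |
| 0.10 | 1.90 | 5.20 | 0.51 |

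The detectable difference in step 4 grows by the square root of the same factor: 0.63 × √1.09 = 0.65, 0.63 × √1.45 = 0.75 and 0.63 × √1.90 = 0.86 (from the unrounded 0.6265). Denominator degrees of freedom are not reduced for the number of clusters, so this is a lenient illustration.

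**The case against.** The strongest reply is that CO2e is a declared outcome of this trial. The Primary Objective section lists it, and the Objective section makes mitigation of climate change one of two goals. Sizing on one of several primary variables is common. The power section says openly that its effect size is for CO2e and nowhere claims 80% for nutrients or activity. All of this stands. A reader might infer that the trial was sized on something foreign to its purpose, or that a CO2e result is of no use to it; the documents support neither. The hypothesis paragraph nevertheless remains without a sized test.

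A reader might also infer that a null result on nutrition or activity would be taken to refute the hypothesis, or that a CO2e gain would be reported as confirming it. The Discussion does not support this. It accepts improvement that is equal to or greater than the control arm's as a potential primary finding, and it keeps CO2e apart from food habits and activity.

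Third, it can be said that low power is not shown. That is correct. The smaller effect sizes above are assumptions, and falling power with smaller effects is true of any trial. The point is that power is unstated for the hypothesised outcomes, not that it is known to be poor.

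Finally, the point touches the absence of a single primary outcome. The two overlap in remedy, but aligning the hypothesis with the sizing is needed even if one primary outcome is named.

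**Conclusion.** The concern holds as a mismatch between sections that should agree. The hypothesis names a more nutritious diet and more physical activity; the sample size was derived for diet CO2e; the primary list includes CO2e among many items but leaves out overall physical activity. The hypothesis as written has no sized test.

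The stated 80% reproduces for CO2e alone, assuming a 2-df arm-by-time F test and independent participants. It should not simply be reaffirmed for a cluster-randomized design: under the assumed cluster size and ICCs it is about 0.77 to 0.51. For nutrition and activity no power can be calculated from the protocol. This should be corrected, but it does not invalidate the trial.

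**What to change.** Align the abstract's Objective, Research Hypothesis, Primary Objective, and Power Calculations and Randomization in one of two ways:

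1. Add diet CO2e to the hypothesis as the confirmatory outcome. Report nutrition and physical activity as estimates with confidence intervals, without a confirmatory claim.
2. Keep the hypothesis. Name one Meal-Q nutrition variable and one Active-Q activity variable as its test, put both in the primary list, and state the effect detectable with 40 per arm, allowing for clustering by office.

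In either case, state that the sample size was derived for CO2e only and treats participants as independent. Give power or detectable effect over a plausible range of cluster sizes and ICCs.

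Date the change and disclose whether pilot data had been seen. Recruitment began in August 2022, 37 of the planned 94 participants had been recruited by June 2024, and the pilot analysis is under way, so an undated choice of outcome could look data-driven.

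The cost is text and a short recalculation, with no extra participants required by the rewording itself. The downside is a narrower confirmatory claim, and under the second option possibly a detectable effect larger than the investigators would wish.
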